## Discussion

The present study focuses on describing an innovative experimental protocol based on cardiovascular safety, scope of research, and distinct experimental control to compose a randomized controlled clinical trial, which aims to investigate the applicability and the effect of a novel combination of training protocols of peripheral muscle atrophy and weakness, functional adaptations and on quality of life in severely ill comatose patients and within after 12 months of hospital discharge.

The innovative initial aspects of the study involved the purpose of optimizing the combination of training protocols for severely ill comatose patients. The first protocol consisted of an adaptation of a recently applied protocol, comprising PM and BFR [37] adjusted to the current BFR recommendations [42], aiming to reduce muscle atrophy and weakness. The second purpose included a novel combination involving electrical stimulation, which is widely applied in ICUs [7, 8], with PM and BFR [37] to prevent muscle atrophy and weakness and maximize the functional adaptations and the quality of life, as well as its return to household and social activities.

In addition to using an innovative combination, the experimental design was modified from the intra-subject design, used by previous studies in the field such as Dirks et al. [59], Barbalho et al. [37], and Chhetri et al. [51], to an inter-subject design. The inter-subject design enables the application of protocols bilaterally, simultaneously, and alternately, which allows the replication of the intensive care clinical practice and preserves the ecological validity and investigation of the maximized effects of training on muscle atrophy and weakness, functional responses, and outcome of quality of life of ICU coma surviving patients.

By replicating the intensive care practice, a combination of PM, BFR, and electrical stimulation applied bilaterally, simultaneously, and even alternately will promote unknown cardiovascular responses, which may be investigated as a guarantee of vital safety of the critical patients during the physiological stress imposed by the exercise. Based on that, the present study aimed to measure the cardiovascular responses during and after the first training session, despite the absence of intercurrence or adverse events reported during passive BFR and BFRp, or electrical isolated stimulation [37, 59].

Concerning the scope of the investigation, in addition to the daily assessment of muscle mass, we also proposed a broad assessment of the strength, physical function, and quality of life of the ICU coma surviving patients. Thus, we suggest not only assessing the isolated muscular system in the ICU, but also monitoring the functional integration of the systems through functional analysis and the outcome of quality of life.

For muscle mass, the option of measuring the MT by ultrasound images was based on the scientific validation of this method, which is quicker and simpler for bedside conditions than the cross-sectional area assessment [91]. Additionally, MT presents lower measurement errors such as the coefficient of variation and the typical error, when compared to the muscle cross-section area. The elevated coefficient of variation and typical errors demonstrate high variability between two consecutive measurements, which precludes the detection of daily changes in muscle mass in comatose patients. As a consequence, non-detection of slight changes could impair the management of muscle atrophy prevention, and therefore, the clinical evolution of the patients [92].

In addition to the assessment of muscle mass, muscle quality was evaluated using the MT_echo_ analysis. This method consists of classifying the ultrasound images through greyscale grading, which varies from 0 to 256, where 0 means low gray coloration and 256, intensive gray coloration and characterizes the presence of edema, fat or healthy muscle tissue [72]. Thus, in addition to muscle mass, ultrasound images can assess muscle quality, which involves not only muscle fibers, but also the presence of inflammatory liquid and/or intramuscular fibrosis acquired from low mobility changes, intensive therapy strategies, and exercise-related muscle damage. Additionally, muscle quality assessment allows normalization of MT to the respective echo intensity. This strategy overlooks changes in edema or fibrosis in the MT results, suggesting that the promoted changes are mainly due to the real effect of resistance training on muscle mass [93].

To test muscle strength, the MRC score was applied, which is the gold standard assessment for global strength [74]. This method was suggested to evaluate the muscle strength of patients that awake from coma until hospital discharge. Thus, we were concerned with monitoring the neuromuscular evolution of the critical patient, targeting it to analyze the effect of training during the whole hospitalization stay.

Consecutively, the physical function measurement was described to evaluate the interaction of the neuromuscular system with the other organic systems. Thus, we suggested applying the PFIT scored while awake from coma and ICU and hospital discharge. In addition, the Barthel Index was suggested to assess physical performance during the recovery process at home, as it is validated for use through telephone contact [80, 94].

Thus, an evaluation of the clinical outcome after 6 and 12 months of hospital discharge was also structured in the system’s functional integration to evaluate the household and social reinsertion of patients surviving ICU coma. The rationale of our choice was based on associating muscle strength loss with the worsening of quality of life [27, 29–31, 95]. From this, the follow-up of the clinical outcome was suggested through the SF-36 questionnaire.

In addition to suggesting a broad and integral approach to neuromuscular and systemic functional assessments, the inclusion criteria and the experimental design were based on the largest possible number of methodological control conditions. Thus, for the inclusion criteria, the preference for comatose adults was essential for better control of the population in question.

More specifically, our objective was to ensure that the muscular evaluation was performed during the longest period of bed restriction, in which muscle atrophy and weakness occurred [15, 17, 32]. Finally, patient admission was based on a moderate to severe coma classification, aiming to avoid different volumes of active contractions and, consequently, different stimuli in muscle protein syntheses, which would promote a high variability in responses to the study of muscular variables.

Regarding the trial design, the inclusion of patients within the first 18 h of coma identification was suggested to promote a higher experimental control. The aim of this was to ensure that there would be enough time to perform the admission procedures and the first training session, before the beginning of the deleterious effects associated with low mobility [15, 16].

Another control that was adopted was the randomization of patients into experimental groups by ranking the characteristics that could impair the between-group comparison. More specifically, a peculiar aspect of intensive care studies is the high variability of the sample characteristics, principally in adult ICUs, where the admission involves non-pediatric patients of both sexes, with all types of clinical severe illness, pre- and post-surgery. Thus, to homogenize the experimental groups, we purposely stratified the participants into quartiles, considering MT and type of disease.

To further enhance trial control, our study also proposed daily assessments involving muscle mass. This strategy enables a detailed and trustworthy monitoring of the training-related responses, which differs from specific evaluations, performed during the pre- and post-training period. In addition, this strategy may be important for the experimental and statistical adequacy of the clinical trial to intensive care, in which daily pre- and post-session assessments allow lower experimental losses. Thus, in the event of unanticipated patient discharge or death, the statistical analysis may include the last assessment data from the previous day.

Despite the positive aspects presented, the study is not without limitations. The inclusion of patients with varied duration of coma (2–6 days of intervention and 2 to 12 days of ICU permanence) may lead to high heterogeneity at both time points. As an alternative, the use of subgroups for the duration of the coma (2–3, 4–5, and 6 days), alertness (1–2, 3–4, and 5–6), and the time of stay in the ICU (3–4, 5–6, 7–8, 9–10, and 11–12) was suggested. Finally, the patients who were not classified in the study groups or in the added subgroups should be included in the clinical trial flowchart, but not in the statistical analysis.

From the promising and novel optimizing association of early mobilization protocols with comatose patients in the ICU, using broad methods of clinical monitoring and methodological control, the present study promoted a wide, integral, innovative, and viable experimental protocol to a future randomized controlled clinical trial, aiming to reproduce new scientific evidence regarding early mobilization in critical care. More specifically, our study enabled the investigation of cardiovascular safety, applicability, and effects of innovative peripheral motor interventions to prevent muscle atrophy and weakness, reduced physical function, and low quality of life, which were monitored since coma until health recovery with 12 months of hospital discharge.

Thus, we expect to contribute to the clinical practice of early passive mobilization in critically comatose patients through the purpose of maximizing the effects of an optimized interventional protocol and, consequently, cooperating for musculoskeletal rehabilitation and functional reinsertion in the home and social activities of survivors of coma in ICUs.

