### Study population

The inclusion, non-inclusion, and exclusion criteria are shown in Table 1. All the criteria will be reevaluated before each training session, according to the clinical specificity of the criteria (Table 1). All non-included patients will be re-evaluated after 18 h of coma, except for patients whose hospitalization is longer than 18 h prior to ICU admission. In conclusion, all patients will be assisted by the ICU physiotherapy team. Additionally, the number of PM sessions or any type of physical therapy intervention in the peripheral muscle will be quantified to control the total volume of stimulus for each patient.

**Table 1 Tab1:** Inclusion, non-inclusion, and exclusion criteria of the study population

Inclusion criteria	Non-inclusion criteria	Exclusion criteria
1. Age of 25 to 55 years	1. Persistent arrhythmia with atrial fibrillation	1. Obese (BMI > 30 kg/m^2^)
2. Scores − 5 or − 4 according to the Richmond Agitation-Sedation Scale (RASS) or 3 to 5 in the Glasgow Comatose Scale	2. Pre-existing atrioventricular block or ventricular tachycardia	2. More than one thromboembolism risk factor
3. Maximal 18 h of coma in ICU admission or during critical care hospitalization	3. Recent acute myocardium infarction	3. Previous venous thrombosis and/or pulmonary embolism
4. Prediction of coma length between 2 and 6 days	4. Provisional or definitive pacemaker	4. Peripheral arterial vascular disease history or suspicion of lower limb arterial insufficiency
5. Prediction of 2 to 12 days of ICU permanence	5. Signals of intracranial hypertension	5. Severe cardiovascular instability and/or use of vasoactive drugs in infusion ≥ 0.5 mcg/kg/min
6. Daily protein consumption standardized for the ICU medical and nutrition teams	6. Neoplasia in chemotherapy treatment	6. Deep coagulopathy (prothrombin time (PT) > 2.5 times the normative values, activated partial thromboplastin time (APTT) > 2 times the normal or platelet count ≤ 50.000/μl)
	7. Non-consolidated fractures	7. Heparin intravenous infusion ≥ 2 UI/ml
		8. Fever or hypothermia
		9. Anemia
		10. Neurodegenerative disease
		11. Musculoskeletal disease

*ICU* intensive care unit

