## Statistical analysis

After data collection, participants will be distributed into subgroups by periods in coma (2, 3–4, 5–6 days), in alertness (1–2, 3–4, 5–6 days), and in ICU permanence (3–4, 5–6, 7–8, 9–10, 11–12 days). The normality of data will be analyzed using the Shapiro-Wilk test. One-way analysis of variance (ANOVA) will be used for intra-group comparisons in T0. A mixed-model analysis will be used for each dependent variable, whereas group and time will be considered as fixed factors and subject as the random factor. In case of significant *F*, the Tukey adjustment will be applied for multiple comparisons. In the event of a non-normal data distribution, a Kruskal-Wallis test will be applied to test for the differences in baseline values and the Friedman test to analyze the repeated measures. The adjusted *p* values will be calculated using the Hommel procedure [48]. Effect sizes between and within groups will be calculated using Cohen’s *d* [89]. The minimal clinically important difference will be assessed with distribution-based methods [90]. The statistical significance will be assessed at *p* < 0.05. All analyses will be performed using R 3.6.2 (The R Project for Statistical Computing, 2019) in R-studio 1.3.443 (RStudio Inc., Boston, MA, USA).

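### Randomised patients who fall outside the duration subgroups are left out of the statistical analysis, although those subgroups are formed from coma, alertness and ICU days observed after randomisation

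*Protocol article*

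**What the plan says.** **Protocol article, Statistical analysis.** Once all data are in, "participants will be distributed into subgroups by periods in coma (2, 3–4, 5–6 days), in alertness (1–2, 3–4, 5–6 days"). A third set of bins covers ICU stay, in two-day steps from 3 to 12 days. The section then plans a mixed model for each dependent variable, with group and time as fixed factors and subject as random. It does not repeat any exclusion.

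**Protocol article, Discussion (limitations paragraph).** Because coma and ICU stay vary in length, the authors suggest "the use of subgroups for the duration of the coma (2–3, 4–5, and 6 days"), with the same alertness and ICU bins as above. The closing sentence deals with patients who have no study group and with those who have no place "in the added subgroups should be included in the clinical trial flowchart, but not in the statistical analysis".

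**Protocol article, Discussion (paragraph just before).** After an unanticipated discharge or death, the analysis may use the previous day's assessment.

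**Protocol article, Table 1.** Patients enter on a predicted coma of 2 to 6 days and on "Prediction of 2 to 12 days of ICU permanence".

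**The concern.** Whether a patient fits a bin is known only after treatment. Training continues until awakening, death or ICU discharge, and these same events fix the days in coma, alert and in the ICU. Dropping randomised patients on such durations means that the analysed arms are no longer the arms that randomisation created. If an intervention alters how long patients stay in coma or in the ICU, or whether they wake, it also alters who is analysed.

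The mixed model is planned for every dependent variable, and Table 2 lists blood pressure, heart rate and SpO2 among the variables. Valid first-session (T1) data could thus be discarded because of what happened to the patient days later. With 39 patients, about 13 per arm if allocation is equal, a few exclusions matter. Two sets of coma cut-points, and an unstated matching rule, also leave choices that could be made after the data are seen.

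**Working it through.** **1. Coverage of the bins**

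| Axis | Eligibility (predicted) | Bins (observed) | Not covered |
|---|---|---|---|
| Coma | 2–6 d | 2, 3–4, 5–6 (Statistical analysis); 2–3, 4–5, 6 (Discussion) | <2 d, >6 d |
| Alertness | none | 1–2, 3–4, 5–6 | 0 d, >6 d |
| ICU stay | 2–12 d | 3–4 up to 11–12 | <3 d, >12 d |

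The two coma schemes span the same 2–6 days, so they exclude the same people. They do group patients differently: a 3-day coma sits with 4 days in one scheme and with 2 days in the other.

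**2. Example patients under the two possible matching rules**

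| Course (coma / alert / ICU days) | Coma bin | Alert bin | ICU bin | One bin enough | All bins needed |
|---|---|---|---|---|---|
| 2 / 0 / 2 | yes | no | no | kept | dropped |
| Death in coma, day 4: 4 / 0 / 4 | yes | no | yes | kept | dropped |
| Death in coma, day 8: 8 / 0 / 8 | no | no | yes | kept | dropped |
| 2 / 7 / 9 | yes | no | yes | kept | dropped |
| 5 / 10 / 15 | yes | no | no | kept | dropped |
| Death in coma, day 1: 1 / 0 / 1 | no | no | no | dropped | dropped |
| 8 / 12 / 20 | no | no | no | dropped | dropped |

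Under either rule some randomised patients are lost. If one bin is enough, only extreme courses go. If all are needed, anyone who never wakes and anyone staying 2 days or more than 12 days goes.

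**3. How far the two rules differ inside the eligible range**

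Take whole-day coma c = 2 to 6 and stay s = c to 12, and assume alert days = s − c. The number of pairs is 11 + 10 + 9 + 8 + 7 = 45.

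- One bin enough: every pair has a coma bin, so 0 of 45 are lost.
- All bins needed: s − c must be 1 to 6 and s must be 3 to 12. That leaves 6 values of s for each c, so 5 × 6 = 30 pairs are kept and 15 are lost: 5 with 0 alert days and 4 + 3 + 2 + 1 = 10 with more than 6.

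These are counts of combinations, not patient rates. The documents give no distribution of durations, and alert days need not equal s − c, since coma may begin during the ICU stay.

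**4. Possible bias (assumed inputs)**

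Let q be the share excluded in an arm and D the outcome difference between excluded and retained patients, taken as equal in both arms. The retained mean differs from the full-arm mean by q × D in size, so the bias in the arm difference is D × (qB − qA) in size.

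- Equal shares: 0.
- 10% versus 30%, D = 0.5 to 1.0 SD: 0.20 × 0.5 = 0.10 to 0.20 × 1.0 = 0.20 SD.
- 10% versus 40%: 0.15 to 0.30 SD.

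**5. Numbers analysed (assumed overall share)**

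The expected number is 39 × (1 − q): 35.1, 31.2, 27.3 and 23.4 for q = 10, 20, 30 and 40%. The binomial chance of at least 10 exclusions, which takes the analysed number below the 30 on which the sample size rationale is based, is 0.004, 0.24, 0.78 and 0.98.

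**The case against.** - **Status of the sentence.** It stands in a limitations paragraph, is phrased as a suggestion, and concerns a pilot. It might also be read as covering only patients in neither a study group nor a subgroup, which would spare everyone randomised. That would make the mention of subgroups idle, because they are formed from participants who already have a group. The sentence is the article's only statement on who is left out of the analysis, and it should not stand as it is.
- **Deaths.** A reader might infer that the rule removes deaths. The text does not go that far: the last-assessment sentence allows data from patients who die to be used, and a death on day 4 fits a coma bin and an ICU bin. The rule *can* remove deaths, and the two sentences need reconciling.
- **Worst courses.** Nor is it shown that the sickest patients are the ones lost. Of the 15 lost pairs in step 3, 10 are patients alert for more than 6 days. The direction is mixed.
- **Safety.** A reader might infer that the primary safety result is biased. T1 data are collected before any bin is known, and the interruption and applicability rules count patients, sessions and events with no restriction to binned patients. If a restricted set were used, 2/13 = 15.4% would meet the 15% rule and 1/12 = 8.3% would not, but nothing says it would be. Only the T1 model comparisons are exposed.
- **Rechecked criteria.** The article says "All the criteria will be reevaluated before each training session", but not that a patient who fails a recheck becomes unclassified.
- **The 30% figure.** The 30% for death or immediate discharge in the sample size rationale belongs to the monthly recruitment estimate. It does not measure exclusions after randomisation.
- **Crossed subgroups.** No section says that the three sets of bins will be crossed.

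These points limit the claim. They do not remove the post-randomisation exclusion itself.

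**Conclusion.** The point holds as a stated rule that excludes randomised patients on durations observed after randomisation. It can bias the arm comparisons, including the mixed-model comparison of T1 cardiovascular outcomes. Bias is a risk here and is not demonstrated. It is zero if the arms lose equal shares of similar patients and treatment does not affect bin membership, and 0.10 to 0.30 SD under the unequal shares assumed above. The documents fix neither the size nor the direction. How many patients are affected depends on a matching rule that the text leaves open. The conflicting coma cut-points, and the unreconciled sentence on the last assessment, are plain inconsistencies that need no assumption.

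**What to change.** 1. Delete the exclusion sentence from the Discussion.
2. State in the Statistical analysis section that every randomised patient is analysed in the allocated arm with the planned mixed model, using the available daily assessments up to death or discharge. This also settles the last-assessment sentence.
3. State that safety and applicability are counted in every patient who started a session.
4. Keep the duration subgroups for description only. Use one set of coma cut-points in both sections, and add open-ended categories so that nobody falls out: coma <2 and >6 days, alertness 0 and >6 days, ICU stay <3 and >12 days.

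The cost is a wording change in two sections. No new data are needed, and the planned model needs no duration bin. The estimates will carry somewhat more heterogeneity in duration, which the time factor already in the model partly addresses. The Trial status section reports recruitment suspended with too few participants, so on that account the change can still precede the analysis.

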## Trial status

This manuscript is based on the most recent version of the protocol (4 April 2020). The study was opened to recruitment at the ReBec site in April 2020, and the first participant was recruited in the same month. Recruitment was expected to be completed in October 2020; however, an insufficient number of participants was recruited due to the current pandemic scenario. In this regard, recruitment was suspended during the pandemic quarantine period in Brazil which explains the delay in submitting the study to this journal.

## Data Availability

The datasets supporting the conclusions of this article are available in the repository of the ReBec (http://www.ensaiosclinicos.gov.br), registration number RBR-2qpyxf.

## Abbreviations

ICU: Intensive care unit
PM: Passive mobilization
BFR: Blood flow restriction
BFRp: Blood flow restriction associated with passive mobilization
BFRpE: Blood flow restriction associated with passive mobilization and combined with electrical stimulation
T0: Baseline
T1: First training session
T2: Last training session
SPIRIT: Standard Protocol Items: Recommendations for Interventional Trials
NRS-2002: Nutritional Risk Screening 2002
SF-36: Medical Outcome Study 36 – Item Short Form Health Survey
MT: Muscle thickness
VL: *Vastus lateralis*
SBP: Systolic blood pressure
SBPc: Central systolic blood pressure
SBPp: Peripheral systolic blood pressure
DBP: Diastolic blood pressure
DBPc: Central diastolic blood pressure
DBPp: Peripheral diastolic blood pressure
HR: Heart rate
MAP: Mean arterial pressure
SpO_2_: Peripheral oxygen saturation
RF: *Rectus femoris*
AT: Anterior tibial
MRC: Medical Research Council
CAM-ICU: Confusion Assessment Method for Intensive Care Units
PFIT: Physical Function in Intensive Care Test Scored
RR: Respiratory rate
MT_echo_: Echo intensity
ANOVA: Analysis of variance
SD: Standard deviation
ReBec: Brazilian Clinical Trial Registry
UFSCar: Federal University of São Carlos
CAPES: Coordination for the Improvement of Higher Education Personnel
LACAP: Cardiopulmonary Physiotherapy Laboratory
MUSCULAB: Laboratory of Neuromuscular Adaptations to Resistance Training
